### Methods for additional analyses (e.g. subgroup analyses) {20b}

Since randomization will be stratified by LOC, supportive analysis of the primary endpoint will be performed using a binary logistic regression model with dependent variable SSI and covariates intervention group and LOC. In addition, the following parameters might influence the outcome, which is why they will be included as model covariates in an additional model:Operation-related risk factors: (a) type of surgery; (b) duration of surgery; (c) NNIS Risk Score, (d) use of wound-edge protectors; (e) intraoperative changing of gloves before skin closure; (f) presence of an enterostomy; (g) administration and timing of antibiotic prophylaxis;Patient-related risk factors: (g) BMI; (h) ASA score; (i) Age; (j) diabetes; (k) smoking; (l) alcohol abuse; (m) Charlson Comorbidity Index, (n) history of SSI; (o) history of radiotherapy; (p) history of chemotherapy, (q) days of hospitalization prior to surgery.

Supportive analysis of the primary endpoint will be performed on the ITT set using multiple imputations for any missing SSI values and on the PP set. Secondary endpoints will be analysed by intervention arm on the ITT set, using appropriate descriptive statistics. Any explorative statistical testing will be performed using a significance level of 5%. The assessment of safety will be based on the frequency of AE/SAE as defined in the protocol within the safety population consisting of all patients randomized into the study.

### Methods in analysis to handle protocol non-adherence and any statistical methods to handle missing data {20c}

Multiple imputations will be used for missing primary endpoint data. All other data will be analysed on a complete-case basis.

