## Statistical methods

### Statistical methods for primary and secondary outcomes {20a}

The intention-to-treat (ITT) set consists of all patients who received irrigation of the abdominal cavity before closure of the abdominal fascia with one of the study solutions. Analysis will be performed as randomized regardless of the actual intervention and regardless of any further medical or surgical treatments. The Per-Protocol (PP) set consists of patients treated according to protocol, excluding any major protocol violations. The PP set will be analysed as treated. The Safety (SA) set will consist of all patients in the ITT set, analysed as treated.

All primary and secondary analyses will be performed on the ITT set. Sensitivity analysis of the primary endpoint will be performed on the PP set. The SA set will be used for the safety analyses. The incidence of SSI within 30 days after surgery will be compared between the two study groups using the one-sided group sequential test of two proportions at the 2.5% significance level with a total of two looks at the data. The primary endpoint analysis will be performed on the ITT set. Since the ITT set includes all patients who were treated in the study regardless of any further medical or surgical treatments, it is expected, that the SSI rates 30 days post-surgery will be available for most patients. Nevertheless, it is possible that some patients do not reach the primary endpoint due to death, withdrawal of informed consent, loss to follow-up, or other unforeseen reasons. Patients who die before day 30 will be considered as having SSI at time of death regardless of the intervention group, unless SSI was documented earlier. All other missing primary endpoint data will be dealt with using multiple imputations based on binary logistic regression models including LOC, ASA, BMI, age, diabetes, type of surgery, duration of surgery, use of wound-edge protectors, and intraoperative changing of gloves.

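### Imputing SSI but leaving covariates to complete cases means the 18-covariate supportive model does not analyse the ITT set it names (minor)

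*Protocol article*

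**What the plan says.** Three sections of the protocol article bear on this.

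- **Missing data {20c}** has two sentences. The first sets the scope of imputation: "Multiple imputations will be used for missing primary endpoint data". The second covers everything else: "All other data will be analysed on a complete-case basis".
- **Additional analyses {20b}** plans a logistic model with intervention group and level of contamination (LOC). It then lists operation-related and patient-related risk factors and says "they will be included as model covariates in an additional model". The analysis set is stated as follows: "Supportive analysis of the primary endpoint will be performed on the ITT set using multiple imputations for any missing SSI values". The analysis is repeated on the per-protocol set.
- **Statistical methods for primary and secondary outcomes {20a}** counts deaths before day 30 as SSI. For the rest it says: "All other missing primary endpoint data will be dealt with using multiple imputations based on binary logistic regression models including LOC, ASA, BMI, age, diabetes", and the list of predictors continues with "type of surgery, duration of surgery, use of wound-edge protectors, and intraoperative changing of gloves". That makes nine predictors.

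No section provides for imputing a covariate.

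**The concern.** The rule in {20c} is stated, not merely left open. It has no wording that limits it to secondary endpoints, and {20b} confirms that imputation is meant for SSI values only. A regression model needs every covariate for every patient it uses. Under the stated rule, one blank among the covariates removes the patient from the additional model, whether SSI was observed or has just been imputed. The model is labelled an ITT analysis but would run on whichever patients have complete covariates.

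Two things are at stake. The estimate would refer to a narrower population than the one named. It would also lose precision in a trial that expects few events. A smaller question arises in {20a}: a logistic imputation model cannot produce a value for a patient with a blank predictor unless that predictor is also filled, and {20c} read literally does not allow that.

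**Working it through.** **The plan's own figures.** Sample size {14} gives SSI rates of 4% and 16%, one-sided alpha 2.5%, 80% power, two looks, a continuity correction, 116 patients per arm (232 in all), 20% drop-out and 290 to be included.

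- Fixed design, unpooled variance: n = (1.960 + 0.842)² × (0.16 × 0.84 + 0.04 × 0.96) / 0.12² = 94.2 per arm.
- Times the group sequential inflation factor of 1.056: 99.5.
- With the continuity correction, (n/4) × (1 + √(1 + 4/(n × 0.12)))²: 115.5, so 116 per arm and 232 in all. This matches.
- 232 / 0.80 = 290. This matches. The planned drop-outs number 290 − 232 = 58.
- Expected SSIs among 290: 145 × 0.04 + 145 × 0.16 = 29.

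**Covariate count.** The operation-related list in {20b} runs from (a) to (g), which is 7. The patient-related list runs from (g) to (q), which is 11. The letter (g) is used twice, so the total is 7 + 11 = 18.

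**Loss from the 18-covariate model.** The documents give no missing rate, so q, the share missing per covariate, is an assumption. With independent blanks, the share dropped is 1 − (1 − q)^18. If instead all blanks fell in the same patients, the share dropped would be q.

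| q (assumed) | share dropped, independent | patients lost of 290 | SSIs lost of 29, pro rata | patients lost if blanks fully cluster (290q) |
|---|---|---|---|---|
| 0.5% | 8.6% | 25 | 2.5 | 1.5 |
| 1% | 16.5% | 48 | 4.8 | 2.9 |
| 2% | 30.5% | 88 | 8.8 | 5.8 |
| 3% | 42.2% | 122 | 12.2 | 8.7 |

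**Patients with both SSI and a predictor missing.** Of the nine predictors in {20a}, LOC is needed for stratified randomisation {16a}, and ASA and age are eligibility items {10}. If these three are always known, six can be blank. As a ceiling, let all 58 drop-outs lack SSI. The number that cannot be imputed is then 58 × (1 − (1 − q)^6):

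- q = 0.5%: 58 × 0.030 = 1.7
- q = 1%: 58 × 0.059 = 3.4
- q = 2%: 58 × 0.114 = 6.6
- q = 3%: 58 × 0.167 = 9.7

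**The LOC-only supportive model.** Its covariates are intervention group and LOC, both fixed at randomisation, so the complete-case rule removes essentially nobody from it.

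**The case against.** **The model is only supportive.** The primary test is an unadjusted comparison of two proportions, and no confirmatory decision rests on the 18-covariate model. Pre-specified complete-case handling of baseline covariates in such a model is transparent and common. This stands and limits the weight of the point, but it does not reconcile the complete-case rule with the ITT label.

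**The size is assumed.** No missing rate is documented. Many covariates are routine record-form items, and queries are to be clarified before the database is closed. Clustered blanks would cost far fewer patients, as the last column of the table shows. This also stands.

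**Joint imputation has its own risk.** Imputing many covariates together with about 29 expected SSIs may be unstable. This is fair, and the fix has to allow for it.

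A reader might also infer two stronger things that the documents do not support.

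- *That the primary analysis loses a material number of ITT patients.* The promise in {20a} is specific: "All other missing primary endpoint data will be dealt with using multiple imputations". It can be read as overriding the residual clause in {20c}, with blank predictors filled as part of the imputation. Most of the nine predictors are eligibility, stratification or mandatory record-form items. The figure of 58 is a ceiling, because deaths count as SSI, the 20% drop-out is not broken down, and {20a} expects SSI to be available for most patients.
- *That the treatment comparison is biased, or that emergency patients drop out selectively.* Recruitment {15} permits same-day inclusion of emergencies but says nothing about gaps in their data, and every patient must be able to give consent. Randomisation takes place at the end of surgery, so nearly all covariates are fixed beforehand and their blanks are unlikely to depend on allocation.

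**Conclusion.** The point holds at minor severity. As written, {20c} removes from the additional supportive model every patient with one blank among 18 covariates, so that model is not the ITT analysis that {20b} says it is. At an assumed, independent missing rate of 0.5% to 3% per covariate, about 25 to 122 of 290 patients would be lost, and fewer if blanks cluster. The cost is precision and a narrower population in a supportive analysis.

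Read literally, {20c} also conflicts with {20a} for a patient missing both SSI and a predictor. Under the ceiling assumptions above this is at most about 3 to 10 patients at 1% to 3% missing, so any effect on the primary analysis is small. The LOC-only supportive model is essentially unaffected, and the sample size is not touched.

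**What to change.** Amend {20c} before any unblinded look at the data, along these lines:

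> *Missing values in covariates used in the imputation model or in the regression models are imputed in the same multiple imputation as SSI, so that every ITT patient enters these analyses. Complete-case analysis applies only to data outside these models.*

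Because only about 29 SSIs are expected, name a fallback in advance: if the joint model is unstable, use a simpler imputation of the baseline covariates.

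The cost is a sentence or two of text, a somewhat larger imputation model and slightly more analysis work. No new data or patients are needed.

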### Plans to give access to the full protocol, participant level-data and statistical code {31c}

The protocol publication will be accessible on the DRKS website (www.drks.de). This includes a summary in lay language for the interested patient community. The full protocol and statistical code can be requested from the authors. Individual participant level data that underline the results reported in this article can be shared after anonymization, with investigators whose proposed use for the data has been approved by an independent review committee identified for this purpose. Proposals can be submitted up to 36 months after publication of the study results.

## Oversight and monitoring

### Composition of the coordinating Centre and trial steering committee {5d}

As this study is planned as a monocentric trial, there is no coordinating centre. The trial steering committee in this setting consist of the study leadership (principal investigator, deputy investigator and coordinating investigator) which is responsible for recruitment of patients and data management. The statistical analysis will be performed by an independent statistician. Trained medical doctors of the local study group will take informed consent. The study leadership will meet once a month to discuss progress and problems regarding the trial. Following the planned interim analysis after 50% of patients are recruited a meeting with the trial statistician and the scientific advisors as well as the funders will be held to discuss the results and consequences. The ethics committee will be informed about the outcome of this meeting. Public involvement is not planned in this study.

### Composition of the data monitoring committee, its role and reporting structure {21a}

In this study setting, a data monitoring committee is not planned, as the intervention poses no additional risks for the patients and is a routine medical procedure.

### Adverse event (AE) reporting and harms {22}

Each adverse event (AE) is to be classified by the investigator according to the Common Terminology Criteria CTCAE V 5.0 [32]. Serious AEs and AEs of special interest are captured and processed until the last visit of the last patient. A final list will be provided to the ethics committee. All documented (S)AEs should be followed to resolution or stabilization. The investigator will be requested to supply as much detailed information as possible regarding the event that is available at the time of the initial contact. The investigator is also required to complete missing or requested information until the (S)AE has resolved or, in the case of permanent impairment, until stabilized. All (S)AEs severity will be additionally graded by the Clavien Dindo Classification of postoperative complications and the CCI.

### Frequency and plans for auditing trial conduct {23}

As this study is comparing two routine surgical procedures, auditing of the trial by external institutions is not required and therefore not planned.

### Plans for communicating important protocol amendments to relevant parties (e.g. trial participants, ethical committees) {25}

Any amendments to the protocol, other than administrative ones (of which the ethics committee will merely be informed), must be reviewed and approved by the ethics committee. The changes will be updated in the clinical register DRKS on a regular basis. If necessary, patient information is updated to inform new participants of the changes.

### Dissemination plans {31a}

After completion of the clinical study, a manuscript of the study results will be prepared for publication in a reputable scientific journal according to the CONSORT statement. For this manuscript, final analyses will be generated from the study database, and it will be subject to review by the principal investigator. The use of professional writers is not intended.

## Discussion

SSI remain one of the most common complications following abdominal visceral surgery (14–25%) [8–10, 25] and dramatically increase the length of hospital stay and treatment costs. Hypothetically, antiseptic IPI at the end of surgery seems to be a pragmatic measure to reduce SSI rates, especially organ/space infections (SSI class III). Currently, the official recommendations on the prophylactic use of IPI and clinical practice vary largely. The existing evidence is low level and does not solely focus on visceral surgery but includes all types of surgery (e.g. orthopaedic- or neurosurgery), which differ substantially in SSI rates and causative microorganisms. However, despite its unproven efficacy, most general and visceral surgeons currently use IPI to prevent SSI. The PAISI study has a pragmatic, 2-armed study design (NaOCl/HOCl 50/50ppm *vs.* Ringer intraoperative peritoneal and wound irrigation). Internal validity and data quality assurance are established by adherence to the SPIRIT guideline regarding recruitment, methods against bias, outcome reporting and documentation. All patients undergoing gastrointestinal or hepatobiliary surgery (LOC II–IV) by laparotomy within 32 months will be screened for this study. Broad inclusion criteria were applied to ensure rapid and sufficient recruitment of the target sample size. The primary endpoint is the incidence of SSI 30 days postoperatively, according to the CDC definition and classification (Table 1) [6]. Since many different SSI definitions have been proposed in the past decades, standardized reporting is crucial for the comparability of studies regarding SSI prevention. The results of this pragmatic study will provide evidence for clinical recommendations regarding the use of antiseptic IPI with NaOCl/HOCl solution to prevent SSI after laparotomy and potentially impact future clinical guidelines. Furthermore, the results will provide a base for future research and provide participating patients the opportunity of an improved treatment.

### Trial status

The first patient was recruited in September 2022, therefore recruitment is planned to be completed approximately by May 2025.

## Data Availability

After completion of the study, individual participant data that underline the results reported in the published article can be shared after anonymization with investigators whose proposed use for the data has been approved by an independent review committee identified for this purpose. Proposals can be submitted up to 36 months after publication of the study results.

## Abbreviations

AE: Adverse event
ASA: American Society of Anaesthesiologists
BMI: Body mass index
CDC: Centre for Disease Control and Prevention
CI: Confidence interval
CTCAE: Common Terminology Criteria for Adverse Events
DRKS: Deutsches Register Klinischer Studien
eCRF: Electronic case report form
ECG: Electrocardiogram
EDTA: Ethylene-diamineteraacetic acid
HOCl: Hypochlorite
ICF: Informed consent form
ICTRP: International Clinical Trials Registry Platform
IPI: Intraperitoneal irrigation
ISF: Investigator site file
ITT: Intention-to-treat
K: Potassium
LOC: Level of contamination
MRI: Klinikum München rechts der Isar
MSZ: Münchner Studienzentrum
Na: Sodium
NaCl: Sodium chlorite
NaOCl: Sodium hypochlorite
PHX: Polyhexanide
PP: Per protocol
PVP-I: Polyvinylpyrrolidone, povidone-iodine
RCT: Randomized controlled trial
SAE: Serious adverse event
SAS: Statistical analysis system
SSI: Surgical site infection
TUM: Technical University of Munich
WHO: World Health Organization
